#### Setting and population

The New York University Langone Medical Center (NYULMC) primary care practices serve patients with a diverse range of socio-demographic characteristics; they range from faculty-based practices with predominately privately insured and/or Medicare patients to Federally Qualified Healthcare Centers with a large Medicaid population (see Table 3). For the pilot study, four practices will be recruited, purposely chosen to reflect key practice setting characteristics (number of full-time providers, depth of support staff, transition to medical home model, insurance mix, patient socio-demographics).

**Table 3 Tab3:** Patient population

Primary care and endocrine practices (N)	78
Demographics	
% Black	15
% Hispanic	43
% Asian	9
% White	25
% Other	8
Patients ≥ 75 with diabetes	5187

Eligible patients within the practice sites will be those aged 76 or older with a diagnosis of diabetes. Patients will be categorized into one of the three glycemic target ranges inspired by the CW recommendation: (1) healthy older adults with an HbA1c target range of 7–7.5% and long life expectancy (defined here as 10+ years); (2) those with moderate comorbidity and a life expectancy of 3+ to 10 years, with a target range of 7.5–8%; and (3) those with multiple comorbidities and life expectancy of less than or equal to 3 years, with a target range of 8–9% [4]. These categories are determined using the life expectancy algorithm described earlier. We expect the majority of patients in the selected population to fall into the “high life expectancy” category (10+ years), as the average life expectancy of a 75-year-old is between 11 and 12 years [53], and about two thirds of patients in the Medicare population have multiple chronic conditions [54–57]. Twenty percent of the population is estimated to be moderately healthy older adults with a medium life expectancy, and 10% are estimated to have an end-stage illness, leading to low life expectancy.

#### Outcomes

Pilot study outcomes will measure implementation as well as provide initial estimates of the BE-EHR modules’ effectiveness.

Process outcomes include utilization, measured via the EHR, such as the percentage of alerts in which the clinician changes the default option. Other outcomes are noted in Table 1. We will also collect qualitative user feedback using user research methods deemed most appropriate (see Table 2) to understand clinicians’ experience with the BE-EHR module and evaluate the specific nudges, as well as explore acceptability, implementation, and adoption issues surrounding them, including assessing their impact on guideline-focused care for older adults with diabetes.

The primary clinical outcome is the percent of eligible patients who are compliant with the AGS CW guideline targeting overtreatment of older adults with diabetes. For each patient, the HbA1c level, diabetes medication prescription status, and life expectancy status will be determined. All patients whose HbA1c are within the target range for their life expectancy status will be considered compliant. Those whose HbA1c are below the target range and who are being treated with a non-metformin agent (i.e., are over-controlled) will be deemed non-compliant. If an eligible patient is on metformin only but the HbA1c is below the upper board of the target range, they will also be deemed non-compliant. These situations are delineated in Table 4. Patient-level compliance outcomes will be aggregated to produce a provider-level compliance rate as a proportion of each provider’s eligible patients.

**Table 4 Tab4:** Choosing Wisely non-compliance categories

Measured HbA1c	Patient category	Current prescription
< 7	Healthy	Non-metformin agent
< 7	Moderate comorbidity	Non-metformin agent
< 7	Shorter life expectancy	Non-metformin agent
7–7.5	Moderate comorbidity	Non-metformin agent
7–7.5	Shorter life expectancy	Non-metformin agent
7.5–8	Shorter life expectancy	Non-metformin agent

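### The primary compliance outcome does not give each patient exactly one class: some patients fall under no rule, and metformin-only patients in range fall under two that conflict

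*Protocol article*

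**What the plan says.** The primary clinical outcome is the percentage of eligible patients who comply with the guideline on overtreatment. The Outcomes section builds it from three sentences and a table:

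- In range: "All patients whose HbA1c are within the target range for their life expectancy status will be considered compliant".
- Below range on another agent: "Those whose HbA1c are below the target range and who are being treated with a non-metformin agent (i.e., are over-controlled) will be deemed non-compliant".
- Metformin only: "If an eligible patient is on metformin only but the HbA1c is below the upper board of the target range", the patient is also non-compliant. The word before the target range is evidently meant to be bound.

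The section adds that "These situations are delineated in Table 4". That table, headed "Choosing Wisely non-compliance categories", has six rows. All are for a non-metformin agent, and none goes above 8.

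The target ranges are in Setting and population: 7–7.5% for healthy patients, 7.5–8% for moderate comorbidity ("those with moderate comorbidity and a life expectancy of 3+ to 10 years, with a target range of 7.5–8") and 8–9% for shorter life expectancy. Utilization rates, under Statistical methods and analysis, makes the indicator binary for each patient and averages it within provider. The denominator is each provider's eligible patients.

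**The concern.** A binary outcome over all eligible patients needs rules that are exhaustive and do not overlap. These rules are neither, so two analysts working from the same EHR extract could report different primary rates and both cite the article.

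The gap above the range also bears on interpretation. The Intervention section has the module suggest stopping or reducing medication below the lower bound, and suggest not adding a prescription above it. If absence from Table 4 means compliant, a patient who moves from below range to above range changes from non-compliant to compliant. Neither the Outcomes section nor the utilization measures in Table 1 would show where that patient ended up. The pilot's clinical estimates are meant to refine the later trial design, so they should be reproducible and readable.

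**Working it through.** The article states no figure to reproduce. The check applies the rules as printed to every combination of patient category, prescription and HbA1c.

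**Inputs.** Target ranges from Setting and population; the three sentences and Table 4 from Outcomes. Ranges are read as closed at both ends, as printed. The HbA1c grid, 5.0 to 12.0 in steps of 0.1, is an assumption.

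**Step 1: class under the three sentences.**

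| Prescription | Category | No class | Both classes |
|---|---|---|---|
| Non-metformin agent | Healthy | 7.6 and up | none |
| | Moderate | 8.1 and up | none |
| | Shorter | 9.1 and up | none |
| Metformin only | Healthy | 7.6 and up | 7.0–7.4 |
| | Moderate | 8.1 and up | 7.5–7.9 |
| | Shorter | 9.1 and up | 8.0–8.9 |
| No agent | Healthy | up to 6.9; 7.6 and up | none |
| | Moderate | up to 7.4; 8.1 and up | none |
| | Shorter | up to 7.9; 9.1 and up | none |

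Table 4 contains none of the cells in the column headed No class.

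**Step 2: metformin only.** The in-range sentence calls these patients compliant. The metformin-only sentence calls them non-compliant at every value short of the upper bound. Only the upper bound itself (7.5, 8.0 or 9.0) escapes the clash. Table 4 has no metformin-only row, so the text also disagrees with the table below range: up to 6.9, 7.4 and 7.9 in the three categories, these patients are non-compliant by sentence and absent from the table.

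**Step 3: shared endpoints, non-metformin agent.** Two cells are compliant by text and non-compliant by Table 4:

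- Moderate comorbidity at 7.5, which is in the 7.5–8 target and in the table's 7–7.5 row.
- Shorter life expectancy at 8.0, which is in the 8–9 target and in the table's 7.5–8 row.

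Healthy at 7.5 and moderate at 8.0 are compliant only. Shorter life expectancy at 7.5 is non-compliant only.

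**Step 4: illustration of the above-range share.** Assumptions: HbA1c is normal with the same distribution in all categories, mean 7.0 to 7.5 and SD 1.0 to 1.3. The mix is 70/20/10; the 20% and 10% are in Setting and population, and 70% is the remainder (100 − 20 − 10). With F the normal distribution function:

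share above range = 1 − [0.7·F(7.5) + 0.2·F(8) + 0.1·F(9)]

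- Mean 7.0, SD 1.0: 1 − [0.7(0.6915) + 0.2(0.8413) + 0.1(0.9772)] = 0.250
- Mean 7.5, SD 1.3: 1 − [0.7(0.5000) + 0.2(0.6497) + 0.1(0.8757)] = 0.432

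Under the same assumptions, with values recorded to 0.1, the ties in step 3 are 0.2·P(7.45–7.55) + 0.1·P(7.95–8.05), or 0.8% to 1.2% of patients. That is an upper bound, because only patients on a non-metformin agent can be in Table 4.

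**The case against.** The best defence is that the outcome has a natural reading. It concerns overtreatment, Table 4 lists the ways to fail, and the indicator is binary, so anyone not listed complies. A patient above target is not over-controlled. This stands as the likelier intention for above-range patients, and counting them as compliant is not in itself an error. But the text never says so, and the reading cannot be applied throughout: it would make every metformin-only patient compliant, against an explicit sentence.

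On the endpoints, the defence is largely right. The text's own term is below the range, a value on the bound is not below it, and the table's dashes may be shorthand.

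A reader might infer more than the document supports:

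- *That the compliance rate is wrong by 25 to 43 percentage points.* Those figures rest on an assumed HbA1c distribution. They also compare the natural reading with one that scores patients above range as breaching an overtreatment guideline.
- *That the module would be declared a success while doing harm.* The pilot is single-arm and reports estimates with 95% confidence intervals. No success threshold is set on compliance, and components are retained on utilization above 30% and on user feedback. The article gives no evidence that patients would be moved above range.
- *That any patient at 7.5% or 8.0% has two classes for want of clear endpoints.* That fault is confined to the two cells in step 3.

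**Conclusion.** The concern holds. The rules for the primary clinical outcome leave two groups without a class (above range on any prescription, and below range on no agent). They give metformin-only patients two classes over nearly all of each target range, and they disagree with Table 4 at two single values. The metformin-only contradiction and the unstated handling of above-range patients matter most; the endpoint ties are minor.

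These conclusions follow from the printed text and need no distributional assumption beyond reading the ranges as closed. The numerical effect on the rate cannot be derived from the article. The 25% to 43% above-range share shows only that the uncovered group could be large under the stated assumptions. Because the Statistical methods section applies this definition as it stands, the fault lies in what the article states and is not a detail left to an analysis plan.

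**What to change.** 1. Reconcile the three sentences, including the metformin-only one, with Table 4 so that each patient has exactly one class. Which clinical rule applies to metformin-only patients is for the investigators to state; this review does not presume it.
2. State how above-range patients, and below-range patients on no agent, count in the rate.
3. Write the Table 4 bands as half-open: <7.0; 7.0 to <7.5; 7.5 to <8.0. A value on the lower bound of the target is then in range, in line with the text's own wording.
4. Report the above-range share beside the compliance rate each time, as a fixed balancing measure.

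The cost is a rewritten paragraph and table and one extra percentage. No new data are needed, because the Outcomes section already has HbA1c, prescription status and life expectancy status determined for each patient. The downside is that the headline rate must be read with a second number.

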### Choosing Wisely guideline for older adults with diabetes

Due to evidence that tight glycemic control in older adults with diabetes may be medically harmful, in 2013 (revised in 2015), the American Geriatrics Society (AGS) developed ten Choosing Wisely (CW) guidelines, of which the third guideline states the following: “Avoid using medications other than metformin to achieve hemoglobin HbA1c<7.5% in most older adults; moderate control is generally better.” [11] Specifically, this guideline incorporates the balance between the number of comorbidities and life expectancy of older adults to provide target ranges for glycemic goals. Reasonable targets include an HbA1c of 7.0–7.5% in healthy, older adults with long life expectancy; 7.5–8.0% for patients with moderate comorbidity and a life expectancy of less than 10 years; and 8.0–9.0% for patients with multiple comorbid conditions and a shorter life expectancy [4, 12].

These recommendations build on previous work categorizing older adults with diabetes into three clinical groups based on health status [13] and have been endorsed by numerous expert panels and guidelines [8, 14, 15]. The target ranges for glycemic control are similar to HbA1c values that have been associated with the best outcomes for older adults with comorbid conditions in observational or modeling studies [16–18]. The American Diabetes Association (ADA) and others have recommended similar health status categories related to HbA1c targets in older adults [8, 14, 15]. Although the ADA guidelines do not identify less aggressive targets for HbA1c [8], other societies, including AGS, recommend similar less aggressive thresholds for glycemic control [15, 19–21].

Despite the CW recommendations, a substantial number of older adults have intensive glycemic control that may not be necessary [22–24]. Additionally, older patients with intensive glycemic control generally do not undergo de-intensification of therapy, suggesting opportunity for improving appropriate care [25]. To combat this problem, the proposed study utilizes a unique approach: using behavioral economics via electronic health records to influence provider behavior with respect to diabetes care for older adults.

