Clinical decisions in accordance with the CW guideline will be drafted and approved by clinical experts on the research team and will guide actions prompted by text and visuals in the CDS modules. Example clinical actions include switching a patient’s medication to metformin, reducing the dose, or removing the prescription of an alternative medication for patients with an HbA1c laboratory value too tightly controlled given their calculated life expectancy. Once the new module has stabilized within the vanguard sites (workflow issues are resolved and clinician usage is stable) (aim 1), the tool will be activated at the pilot sites (aim 2).

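### The primary clinical outcome gives in-range metformin-only patients two opposite classes, and Table 4 has no row for the metformin-only rule it is said to set out

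*Protocol article*

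**What the plan says.** The Outcomes section under Aim 2 builds the primary clinical outcome, the percentage of eligible patients who comply with the guideline, from three rules:

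- **Rule A (in range):** "All patients whose HbA1c are within the target range for their life expectancy status will be considered compliant".
- **Rule B (below range, other agents):** "Those whose HbA1c are below the target range and who are being treated with a non-metformin agent (i.e., are over-controlled) will be deemed non-compliant".
- **Rule C (metformin only):** an eligible patient "on metformin only but the HbA1c is below the upper board of the target range, they will also be deemed non-compliant".

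The text then states: "These situations are delineated in Table 4". Table 4, titled "Choosing Wisely non-compliance categories", has six rows, and each gives a non-metformin agent as the current prescription.

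The guideline is quoted in the Background as "Avoid using medications other than metformin to achieve hemoglobin HbA1c<7.5% in most older adults". The section on algorithms for activating the CDS lists, as example actions for patients controlled too tightly, switching a patient's "medication to metformin, reducing the dose, or removing the prescription of an alternative medication". The Intervention section adds three prompts: metformin as a default where appropriate, no new prescription when HbA1c is above the lower bound, and stopping or reducing the medication when it is below. The last prompt is not limited to non-metformin agents.

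The Utilization rates section carries this patient-level definition into the provider-level compliance rate.

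**The concern.** Rules A and C cannot both be applied to a metformin-only patient who is in range. Rule C also has no counterpart in the table cited for it. It runs against the quoted guideline, because it sets a higher hurdle for the drug the guideline exempts than for the drugs it warns about.

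Two programmers working from this text could code different outcomes, and either could defend the choice. The compliance rate is the pilot's main clinical estimate. The article says the pilot estimates will be used to refine the design of a later trial, and that the pilot results will inform whether to go on to one. A level that depends on which sentence is coded does not serve those purposes.

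**Working it through.** The documents give no compliance figure to reproduce, so the check has three parts: classify every type of patient under each rule, trace what happens when the module's prompts are followed, and size the effect on the rate.

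**1. Classification.** Cross three patient categories with five HbA1c bands (<7, 7–7.5, 7.5–8, 8–9, >9) and two treatment states (non-metformin agent, metformin only). The target ranges come from Setting and population.

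Rule B makes 1 + 2 + 3 = 6 non-metformin cells non-compliant. These are exactly the six rows of Table 4, so rule B and the table agree. Rule C gives:

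| Category (range) | Metformin-only bands non-compliant under rule C | Of these, in range and so compliant under rule A | Metformin-only rows in Table 4 |
|---|---|---|---|
| Healthy (7–7.5) | <7, 7–7.5 | 7–7.5 | none |
| Moderate comorbidity (7.5–8) | <7, 7–7.5, 7.5–8 | 7.5–8 | none |
| Shorter life expectancy (8–9) | <7, 7–7.5, 7.5–8, 8–9 | 8–9 | none |

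Rule C marks 2 + 3 + 4 = 9 cells, and Table 4 lists none of them. Three of the nine contradict rule A directly. The other 9 − 3 = 6 are below range; they conflict with Table 4 and the quoted guideline but not with rule A. If the upper bound is read as a slip for the lower bound, the three direct contradictions disappear, but the six cells missing from Table 4 remain.

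**2. Following the prompts.**

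- A patient below range on a non-metformin agent is non-compliant under rule B. After a switch to metformin only, rule C keeps the patient non-compliant until HbA1c reaches the upper bound. In the healthy group, a rise from 6.8% to 7.2% brings the patient into range and still earns no credit under rule C.
- A metformin-only patient in range, for whom the clinician accepts the prompt not to add a drug, is a failure under rule C.
- For a metformin-only patient below range, the module may suggest stopping or reducing the medication. A non-compliant label is not clearly at odds with the module there.

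**3. Size.** The 20% and 10% for the medium and low life-expectancy groups are stated in Setting and population; 70% is the remainder. The following are assumptions: HbA1c is normal with mean 7.0–7.5 and SD 1.0–1.3, with the same distribution in every category and treatment group, and a share m = 0.20–0.40 of patients is on metformin only. With F the HbA1c distribution function:

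- share below own upper bound: U = 0.7·F(7.5) + 0.2·F(8) + 0.1·F(9)
- share below own lower bound: L = 0.7·F(7) + 0.2·F(7.5) + 0.1·F(8)

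For mean 7.0 and SD 1.0:

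- U = 0.7(0.6915) + 0.2(0.8413) + 0.1(0.9772) = 0.750
- L = 0.7(0.5000) + 0.2(0.6915) + 0.1(0.8413) = 0.572

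| Mean, SD | U | L |
|---|---|---|
| 7.0, 1.0 | 0.750 | 0.572 |
| 7.0, 1.3 | 0.704 | 0.558 |
| 7.5, 1.0 | 0.582 | 0.385 |
| 7.5, 1.3 | 0.567 | 0.410 |

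The fall in compliance relative to Table 4 is:

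- if rule C overrides rule A, m·U: from 0.20 × 0.567 = 11 points to 0.40 × 0.750 = 30 points
- if rule A prevails for in-range patients, m·L: from 0.20 × 0.385 = 8 points to 0.40 × 0.572 = 23 points

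**The case against.** The best defence is that rule C is a slip. The phrase upper board is plainly garbled, and the sentence may have been meant to say compliant. Read that way, rules A and B and Table 4 fit together. This is plausible, but the article does not say so, and the analysis section applies the definition as written. Correcting the bound alone does not restore agreement with Table 4.

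Three further objections stand, and they limit the point.

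- **Reversal.** A reader might infer that a clinician who follows the prompt and switches an over-controlled patient to metformin turns a complier into a non-complier. The documents do not support this. That patient was already non-compliant under rule B and Table 4, and the switch only fails to earn credit.
- **Bias in an effect.** A reader might infer that the measured effect is biased against the module. Aim 2 is a single-arm, unpowered pilot that summarises compliance rates with confidence intervals, and no between-group effect is estimated. Pruning uses utilization, not compliance. What is shown is a shift in a level. For the same reason, the roughly 5–7% reduction in antibiotic prescribing cited in the Background is not a comparable yardstick.
- **Metformin below range.** The Intervention section treats HbA1c below the lower bound as too tightly controlled without exempting metformin. The article therefore does not settle that such patients must count as compliant.

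The pilot status does not remove the problem, because a descriptive rate also needs one definition.

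**Conclusion.** The primary clinical outcome is defined inconsistently and must be corrected. Two facts need no assumptions: in-range metformin-only patients receive both classes, and none of the nine metformin-only cells covered by rule C appears in the table said to set them out. The rule also runs against the quoted guideline.

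The size depends on a patient mix the documents do not report. Under the stated HbA1c and drug-share assumptions, the compliance level falls by about 8–23 points if the in-range sentence prevails and 11–30 points if the metformin sentence does. With a different mix, the fall equals whatever share of eligible patients is metformin-only and caught by the rule.

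The conflict with the module's advice is partial. It covers missing credit after a switch to metformin, and in-range metformin-only patients for whom no drug was added. It does not clearly extend to metformin-only patients below range.

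**What to change.** Before the EHR outcome report is programmed, reconcile the metformin-only sentence, the in-range sentence, Table 4, the quoted guideline and the module logic in the Intervention section, so that each patient has exactly one class and text and table agree. There are two consistent routes, and the sponsor must choose according to what was intended:

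- **Remove the metformin-only sentence.** The non-compliant cells then reproduce Table 4 exactly. State the class of metformin-only patients below range explicitly, since no remaining sentence names them.
- **Keep metformin-only patients below range as non-compliant.** Add rows for them to Table 4, and correct the upper bound so that the rule no longer overlaps the in-range rule. Explain how this fits the guideline as quoted.

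The cost is one sentence, possibly some table rows, and a line of outcome code. No new data are needed, since HbA1c, prescription status and life-expectancy category are already to be determined for each patient.

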##### Identification of behavioral economic approaches and module opportunities and utilization measures

Initially, the BE and CDS literature will be further reviewed and candidate approaches selected for evaluation by the research team. Based on prior work and the current literature, Table 1 outlines example BE concepts and relevant CDS tools to support the implementation of each BE approach, along with utilization measures available to assess process outcomes.

**Table 1 Tab1:** Behavioral economic strategies and associated module opportunity examples

BE strategy	Module opportunity	Utilization measure
Suggest alternatives [48]	Alert suggests metformin when trying to prescribe other diabetes medication in CW eligible patient	Percentage of eligible alerts where alternative is selected
Accountable justification [48]	Subcomponent of alert asking for justification if prescribing diabetes medication other than metformin	Percentage of eligible alerts where justification is provided (vs. only “clicked through”)
Defaults [30, 49]	Default all diabetes management order sets to suggest metformin in eligible patients	Percentage of order sets where clinician changes the default option
Anchoring [50]	Update HbA1c lab reports for CW eligible patients to show less aggressive treatment goals	Qualitative feedback and percentage of CW compliant patients pre- and post implementation update
Peer comparisons/norming [48, 51]	Modify clinician quality and safety dashboard to visualize diabetes management peer comparisons with color codes to indicate relative performance	Number of views of the peer comparison dashboard
Availability bias [30]	Medication preference list prioritizes metformin	Number of prescriptions for metformin initiated from preference list

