### Statistical methods and analysis

#### Utilization rates

Utilization rates will be estimated for each provider for every BE module component to which they apply (see Table 1); these rates will be summarized across physicians with 95% confidence intervals. To assess clinical value, each patient will be classified as CW compliant or not using the definition above; this indicator will be averaged across patients within a provider to calculate a provider-level compliance rate. These will also be summarized with 95% confidence intervals. The pilot study will provide critical estimates of utilization rates and clinical outcomes, allowing for refinement of the clinical trial design (Additional file 1). Specifically, following completion of the pilot study, the pruning decisions described below can be made to eliminate less effective approaches and guide future module development decisions.

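### The primary clinical outcome is defined inconsistently for metformin-only patients: one sentence of the Outcomes section conflicts with the in-range rule and with Table 4

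*Protocol article*

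**What the plan says.** The primary clinical outcome is the percentage of eligible patients who comply with the Choosing Wisely recommendation. It is built patient by patient: "For each patient, the HbA1c level, diabetes medication prescription status, and life expectancy status will be determined". The Outcomes section of the protocol article then gives three rules in sequence.

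- In range: "All patients whose HbA1c are within the target range for their life expectancy status will be considered compliant". Drug is not mentioned.
- Below range on another drug: "Those whose HbA1c are below the target range and who are being treated with a non-metformin agent" are non-compliant.
- Metformin only: a patient who is "on metformin only but the HbA1c is below the upper board of the target range, they will also be deemed non-compliant".

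The paragraph continues: "These situations are delineated in Table 4". Table 4 has six rows of non-compliance, and each gives a non-metformin agent as the current prescription. No row covers metformin alone.

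The target ranges, under Setting and population, are 7–7.5% (healthy), 7.5–8% (moderate comorbidity) and 8–9% (shorter life expectancy). The recommendation itself, quoted in the Background, reads: "Avoid using medications other than metformin to achieve hemoglobin HbA1c<7.5% in most older adults". In the Utilization rates section, "each patient will be classified as CW compliant or not using the definition above", and the result is averaged within provider.

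**The concern.** The third rule gives a different answer from the first for a metformin-only patient in range, and a different answer from Table 4 for any metformin-only patient below the upper bound. Two analysts working from the same paragraph could therefore report different values of the primary clinical outcome from identical data.

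The conflict falls on the group that the module tries to enlarge. Switching a patient to metformin is one of the example clinical actions in the section on algorithms, and one utilization measure in Table 1 is "Number of prescriptions for metformin initiated from preference list". Under the metformin-only sentence, an over-controlled patient who is switched as encouraged and stays below range is a failure before and after the switch. Under Table 4 that patient stops being one. The pilot's estimates of clinical outcomes are meant to help refine the later trial's design, so an understated compliance rate would carry forward.

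**Working it through.** **Inputs.** Target ranges from Setting and population; the three rules and Table 4 from Outcomes. Cells are 3 patient categories × 5 HbA1c bands (<7, 7–7.5, 7.5–8, 8–9, >9) × 2 prescription states (metformin only; non-metformin agent) = 30. Exact boundary values such as 7.5 were not assessed and do not affect the result.

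**Patients on a non-metformin agent.** Bands below the lower bound: healthy 1, moderate 2, shorter 3, total 6. These are exactly the six rows of Table 4, so text and table agree.

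**Patients on metformin only.**

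| Category | Below range | In range | Below upper bound |
|---|---|---|---|
| Healthy | 1 (<7) | 1 (7–7.5) | 2 |
| Moderate comorbidity | 2 (<7, 7–7.5) | 1 (7.5–8) | 3 |
| Shorter life expectancy | 3 (<7, 7–7.5, 7.5–8) | 1 (8–9) | 4 |
| Total | 6 | 3 | 9 |

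- Metformin-only sentence: non-compliant in 9 cells.
- Table 4: non-compliant in 0 cells, so all 9 conflict.
- In-range sentence: compliant in the 3 in-range cells, so 3 conflict. It is silent on the other 6.

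**Effect on the rate.** Take a patient outside the Table 4 rows as compliant. Among eligible patients, let p be the share in a Table 4 row, a the share on metformin only and below the lower bound, and b the share on metformin only and in range.

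- Table 4: 1 − p.
- Text, in-range sentence governing the 3 cells: 1 − p − a. Gap to Table 4 = a.
- Text, metformin-only sentence governing them: 1 − p − a − b. Gap = a + b.

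The gap therefore lies between a and a + b. The article gives neither. If a + b were 5%, 10%, 20% or 30% (assumed values), the upper end would be 5, 10, 20 or 30 percentage points; the lower end depends on how that share splits between a and b.

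**Illustration (all figures assumed).** A provider has 20 eligible patients, none on metformin only and 5 non-compliant: 15/20 = 75%. Three of the 5 are switched to metformin only.

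| After the switch, the three are | Table 4 | Text, in-range sentence governs | Text, metformin-only sentence governs |
|---|---|---|---|
| still below range | 18/20 = 90% | 15/20 = 75% | 15/20 = 75% |
| in range | 18/20 = 90% | 18/20 = 90% | 15/20 = 75% |

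In the first row both readings of the text miss the change. In the second, the answer depends on which sentence is programmed.

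**After the fix.** With the metformin-only sentence deleted or reversed, conflicts fall from 3 to 0 with the in-range sentence and from 9 to 0 with Table 4.

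**The case against.** The strongest reply is that this is a wording slip. The same sentence contains another (board for bound), and if its last word became compliant it would agree with the in-range sentence, with all six rows of Table 4 and with the guideline. The paragraph also points to Table 4, so a careful analyst has a clear definition to program. Much of this stands: a slip is the likeliest explanation, and it is fairer to call the matter an inconsistency than a deliberate design choice. But the statement is explicit, it sits in the operative outcome rule, and nothing in the article says that the table overrides the text.

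A second reply concerns consequences. This is a single-arm pilot giving preliminary estimates, and the Limitations section says that an adequately powered study was out of scope. The pruning decisions rest on a 30% utilization threshold and qualitative feedback, not on compliance. That also stands: no stated decision rule turns on this rate. It remains the named primary clinical outcome, and estimating it is a stated purpose of the pilot.

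A reader might infer more than the article supports:

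- That the text reverses the guideline by being stricter on metformin only (9 cells) than on other drugs (6). This requires the metformin-only sentence to override the in-range sentence. If the in-range sentence governs, the count is 6 against 6: the text then ignores the guideline's exception for metformin but does not reverse it.
- That a patient in range on another drug who is switched with HbA1c unchanged becomes non-compliant. The in-range sentence says otherwise, and the article does not settle which sentence wins.
- That the stop-or-reduce prompt in the Intervention section must also be rewritten because it names no drug. For patients on a non-metformin agent, its condition is met in the same six cells as Table 4. Whether it should also fire for a metformin-only patient is a clinical choice, separate from the outcome definition.

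**Conclusion.** The inconsistency is real and should be fixed. It is confined to metformin-only patients: 3 cells against the in-range sentence and 9 against Table 4, with full agreement for patients on a non-metformin agent. Table 4 and the quoted guideline show which reading is right.

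As written, the compliance rate would be lower than under Table 4 by at least the share of eligible patients on metformin only and below their lower bound, and by at most the share on metformin only and below their upper bound. It would be wrong to equate the gap with the larger share, because that settles the three in-range cells in favour of one of two contradictory sentences. The size in percentage points cannot be derived from the article. The bounds assume that a patient outside the Table 4 rows counts as compliant.

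**What to change.** In the Outcomes section, delete the metformin-only sentence, or change it to say that an eligible patient on metformin only with HbA1c below the upper bound is deemed compliant. The change is slightly clearer than deletion, because it classifies the below-range metformin-only patient in words and not only by absence from Table 4. Either way, a patient is then non-compliant only if HbA1c is below the lower bound and the current prescription includes a non-metformin agent, as in Table 4.

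The cost is one sentence. HbA1c, prescription status and life expectancy category are already determined for each patient, so no new data are needed. The prompt logic in the Intervention section can stay as it is.
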